## 2.2 Research hypotheses

Our working hypotheses are that the systematic offering of SARS-CoV-2 screening by rapid emergency tests performed by nursing teams, combined with current diagnostic practice in patients with signs suggestive of Covid-19, would be superior to the control strategy and would allow:

- testing for rare or asymptomatic forms of SARS-CoV-2 infection, particularly in people who may escape other screening schemes, and thus improve the control of SARS-CoV-2 circulation in the Paris Metropolitan area, and compare the positivity rate among asymptomatic patients in the study to that of the Paris Metropolitan area region, while expecting to obtain a higher rate in the emergency department population,

- to study the sociodemographic, behavioural factors and practices associated with SARS-CoV-2 infection in the population tested in the emergency department compared to those captured by other schemes (ComCor and COVISAN),
- estimating, by modelling, the incidence of new SARS-CoV-2 infections in the Paris Metropolitan area during the study period,
- to limit the risks of transmission of persons tested positive through the immediate and direct activation of the COVISAN scheme facilitating the steps of isolation, tracing, and source search.

## 2.3 Description of the population to be studied and justification of its choice

The Paris Metropolitan area is a region of metropolitan France with a high prevalence of SARS-CoV-2. According to the SIVIC data of 26 November 2020, the incidence rate in the Paris Metropolitan area is 115 per 100,000 inhabitants compared to 151 per 100,000 at the national level. There are departmental variations with an incidence in Paris of 90, in Seine Saint Denis at 142, the Val de Marne at 153, the Hauts de Seine at 108.

Of the 18 DEPIST study sites, 17 sites agreed to participate in the DEPIST-COVID study (see addendum 1). According to the data collected from the department heads during the week of 16 November 2020, emergency departments currently use PCR or RT-LAMP tests mainly for diagnosis purposes for patients with symptoms suggestive of SARS-CoV-2 or as screening for patients who need to be hospitalised for another reason before being transferred to the hospital department (to avoid hospital clusters), an average of 30 tests per day per department. The sites do not report using antigen testing.

During the previous 2 research projects, effective collaboration had been established with these sites, identified on their recruitment capacities and motivation.

## 2.4 Description of procedures performed or products used in accordance with their current use

In the context of the current pandemic, the health authorities recommend increasing the offer of SARS-CoV-2 testing. Thus, a decree of 24/07/2020 authorises nurses to perform, without medical prescription, nasopharyngeal sampling procedures for the screening of SARS-CoV-2 infection; trained caregivers are also authorised to do so under the responsibility of a physician or qualified nurse from their institution.

## 2.5 Description of the acts and procedures added by the research

The start of the study evaluation periods (i.e. control strategy period and intervention strategy period during which SARS-CoV-2 screening will be offered by nurses) will be randomly assigned for each site following a “cluster and crossover per period” randomisation.

During the intervention strategy period, the proposal of a self-administered questionnaire will be the other procedure added by the research (see addendum 2). The questionnaire concerns SARS-CoV-2 symptoms, contagion possibilities and situations at risk of exposure, as well as sociodemographic characteristics. It was developed by the research team from other questionnaires currently used in France (SocialCov and ComCor questionnaires, Pasteur Institute) or elsewhere .

Regardless of the answers to the questionnaire, SARS-CoV-2 screening by nasopharyngeal sampling will be offered by the triage nurse (*infirmier organisateur de l'accueil*, IOA) or the nurse in the cubicle.

A multiplex PCR test for symptomatic patients or an RT-LAMP test for asymptomatic patients will be performed, according to the symptomatology reported in the self-questionnaire.

During this period, the doctor may also offer a test to the patient if he/she has not already been offered by the nurse.

After performing a test, the patient will be treated according to the circuit defined in each hospital.

In the event of a positive test, if the patient is hospitalised, his/her care will be carried out according to the circuit defined by each hospital. Non-hospitalised patients will be referred to COVISAN or the usual department for follow-up and contact tracing. In the event of a negative test, the usual emergency procedure will follow.

For patients with a positive SARS-CoV-2 test and who have not completed the DEPIST-COVID self-administered questionnaire, a subsequent telephone follow-up will be performed to retrieve their profile based on the questions in the self-administered questionnaire. Patients will be accompanied by the research staff to complete the ComCor questionnaire of the Pasteur Institute to facilitate the study of sociodemographic, behavioural factors and practices associated with SARS-CoV-2 infection.

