|                             | 
A self-administered questionnaire on SARS-CoV-2 symptoms, possible contact, exposure risk situations, as well as socio-demographic characteristics will be offered to patients enrolled who are able to complete it.
 
If necessary, the nurse will help the patient complete the questionnaire.
 
In the triage room or in a cubicle, SARS-CoV-2 screening will be offered by the nurse regardless of the answer to the questionnaire.
 
A nasopharyngeal sample will be taken by the nurse in accordance with the personal protection measures recommended in the hospital protocol, with the exception of patients who cannot have a nasopharyngeal sample (contraindication of thrombocytopenia or ENT malformation leading to an oropharyngeal sample being offered). Trained caregivers will also be authorised to carry it out under the responsibility of a physician or registered nurse at their institution.
 
The choice of test will be determined based on the presence of suggestive symptoms.
 
For patients with symptoms suggestive of SARS-CoV-2 infection, known as “symptomatic”: a multiplex PCR test will be performed with result in 75 minutes.
 
For patients with no symptoms suggestive of SARS-CoV-2 infection, known as “asymptomatic”: an RT-LAMP test will be performed.
 
In the event of a positive test, the patient will be treated according to the circuit defined by each hospital. Outpatients will be referred to the usual department for follow-up and contact tracing.
 
In the event of a negative test, the usual emergency procedure will follow.
 
A subsequent telephone follow-up of patients will be performed to retrieve their profile.
 
Control strategy
 
The doctor offers a SARS-CoV-2 test according to current recommendations. Patients with a positive test will be asked to complete the questionnaire. Patients who have not completed it will be contacted by telephone to answer the DEPIST-COVID questionnaire by telephone.
 |

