### 6.1 Research schedule

- Enrolment start date: January 2021
- Duration of the inclusion period: 2 months (with possibility of extension to 15 days per period + wash-out)
- Duration of participation for a patient: 1 day (visit to the ED) + telephone call within 15 days  $\pm$  10 to retrieve patient profile data if necessary
- Number of sites: 18 emergency departments of the Paris Metropolitan area of which 17 are participants in the DEPIST (HIV) study and including 13 emergency departments of the AP-HP

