| Offer of SARS-CoV-2 testing by the nurse or caregiver, regardless of the answer to the questionnaire                                                                                                                                                                                 | R                                                                                                               |                                                                                                                         |
| Nasopharyngeal sampling performed and result provided                                                                                                                                                                                                                                | R (In addition to usual practice, a nasopharyngeal sample RT-LAMP test is performed for asymptomatic patients.) | S
(usual practice based primarily on a SARS-CoV-2 diagnosis by PCR in hospitalised patients or symptomatic patients) |
| For patients tested SARS-CoV-2+ who have not completed questionnaires: collection of data from the DEPIST-COVID questionnaire during a telephone call.                                                                                                                               | R                                                                                                               | R                                                                                                                       |
| Assistance in completing a ComCor questionnaire from the Pasteur Institute in paper format (see addendum 6) (or online on the study site as possible), in order to facilitate the study of sociodemographic, behavioural factors and practices associated with SARS-CoV-2 infection. | R                                                                                                               |                                                                                                                         |

*S: usual practice in the context of Care; R: practice added by the Research*

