##### Secondary endpoints analyses

- The proportion of patients tested positive for SARS-CoV-2 among the asymptomatic or paucisymptomatic patients tested by nurses and that in the Paris Metropolitan area at the same period will be compared using an asymptotic Wald test.  
The proportion obtained in each emergency department will be compared to that of the department's IRIS geographical area using an asymptotic Wald test. The same comparisons will be made across the entire tested population.
- The feasibility of the testing will be described: proportion of patients who have completed the questionnaire, proportion of offered, accepted and performed tests, and notified of the SARS-CoV-2 result and staff involved (nurses, caregivers, doctors, others),
- The proportion of patients tested positive for SARS-CoV-2 among the patients tested by nurses, the proportion of asymptomatic patients among the patients tested by nurses and the proportion of asymptomatic patients among the patients tested positive for SARS-CoV-2 will be described.

|                        |              |
|------------------------|--------------|
| Study                  | DEPIST-COVID |
| Promotion/gestion code | APHP201625   |
| Study coordinator      | [name]   |

- The symptoms of patients tested positive for SARS-CoV-2 will be described in the patients completed the questionnaire.
- Exposure factors will be described using the items in the DEPIST-COVID questionnaire. Among patients tested, the exposure factors associated with the positivity of the SARS-CoV-2 test will be analysed using a generalised linear mixed model (binomial distribution or other distribution adapted to the data). The exposure factors will be considered as fixed effects and the site as a random intercept. Other fixed variables could be added to the model if appropriate.
- The sociodemographic, behavioural and practical factors of diagnosed patients associated with positive SARS-CoV-2 infection will be described for the schemes (DEPIST-COVID, ComCor) according to the types of variables (proportion, mean and standard deviation or median, Q1-Q3) and presented with their 95% confidence interval. If appropriate, the factors will also be analysed in the population of DEPIST-COVID cases (positive tested patients) and controls (negative and matched tested patients).

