### **Secondary endpoints analyses**

- Factors associated with performing systematic nurse-driven screening will be analysed in patients who had screening offer using a generalised linear mixed model (binomial distribution) with the centre as a random intercept and the patient characteristics as fixed effects.

- The factors associated with new SARS-CoV-2 diagnoses will be analysed using a generalised linear mixed model (binomial distribution) with the centre as a random intercept and patient characteristics as fixed effects.

- The proportions of new SARS-CoV-2 diagnoses through systematic nurse-driven screening overall and per ED, and proportion among all patients tested in EDs, will be compared to the proportion of positive tests among adults tested in the geographical departments of the Paris Metropolitan area using the Miettinen-Nurminen method for risk difference and 95% CI estimations.

[figure not shown]

Coller ici l'étiquette patient

N° DOSSIER :

\_\_\_\_\_  
Centre

\_\_\_\_\_  
Patient

PLEASE FILL OUT THIS QUESTIONNAIRE BY CHECKING THE SQUARE  
CORRESPONDING TO YOUR RESPONSE [figure not shown]

1 You are:

☐ male ☐ female

2 What is your date of birth?

Month Year

3 Do you have symptoms suggestive of Covid-19?

☐ Yes ☐ No

> If yes, please precise:

☐ Fever (>38°C)  
or fever sensation

☐ Cough

☐ Loss of smell

☐ Muscular pain

☐ Unusual fatigue

☐ Breathing difficulty  
(shortness of breath)

☐ Loss of taste

☐ Other

☐ Headache

☐ Sore throat

☐ Diarrhoea

☐ Runny nose

> If yes, date of first symptoms:

Day Month Year

4 What is your postcode?

5 In which country were you born?

☐ France

☐ Other

Please specify your country of birth:

6 Until what age did you study?

years

7 Currently (over the last month):

☐ You work

☐ You do not work

☐ You are seeking employment

☐ You are a student

> If you work:

• Do you work away from home?:

☐ Yes

☐ No

☐ Partially

• Does your occupation expose you to contacts with:

- Members of the public?

☐ Yes

☐ No

- Sick persons?

☐ Yes

☐ No

8 What is your medical coverage:

☐ Social security without supplementary health insurance

☐ CMU (Universal medical cover)

☐ Social security with supplementary health insurance

☐ AME (State medical assistance)

☐ No medical coverage

☐ Other

9 Do you suffer from a chronic disease (diabetes, high blood pressure, angina pectoris, chronic bronchitis, asthma or chronic respiratory disease)?

☐ Yes

☐ No

10 Do you currently smoke cigarettes?

☐ Yes

☐ No

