## OVER THE LAST 10 DAYS:

14 Apart from at home, have you always worn a mask? ☐ Yes ☐ No

---

15 Have you always worn a mask with friends or family that you do not live with? ☐ Yes ☐ No

---

16 Have you always kept within at least one meter in the following situations?

- At work or school: ☐ Yes ☐ No
- With friends or family: ☐ Yes ☐ No

---

17 Have you been in close contact with someone who has tested positive for Covid-19?

☐ Yes, 1-2 times ☐ Yes, 3 times or more ☐ No

> If yes, please precise:

☐ Family who you live with ☐ Family who you do not live with ☐ Friend

☐ Colleague ☐ Notification by the TousAntiCovid app ☐ Other

---

18 Have you been out of your home:

- For work? ☐ Yes, 1-2 times ☐ Yes, 3 times or more ☐ No
- For your studies? ☐ Yes, 1-2 times ☐ Yes, 3 times or more ☐ No

---

19 Have you used public transport? ☐ Yes, 1-2 times ☐ Yes, 3 times or more ☐ No

---

20 Have you been to a restaurant or a bar? ☐ Yes, 1-2 times ☐ Yes, 3 times or more ☐ No

---

21 Have you been to a gym/sports hall? ☐ Yes, 1-2 times ☐ Yes, 3 times or more ☐ No

---

22 Have you been to a gathering of more than 5 people?

☐ Yes, 1-2 times ☐ Yes, 3 times or more ☐ No

> If yes, for the busiest gathering:

- What type of gathering was it?

☐ For work ☐ At school/university ☐ A cultural site (cinema, theatre)

☐ A religious gathering ☐ A private gathering (friends/family) ☐ Other

- Was the gathering in: ☐ a Closed space ☐ An open space ☐ Both
- How many people were there: ☐ 5-10 ☐ 10-20 ☐ 20-50 ☐ > 50 people
- Were you wearing a mask? ☐ Yes ☐ No

> If yes: did you wear the mask the whole time? ☐ Yes ☐ No

- Were you more than one meter away from every person? ☐ Yes ☐ No

---

23 Have you been hospitalised? ☐ Yes, 1-2 times ☐ Yes, 3 times or more ☐ No

---

24 Have you taken a Covid-19 screening test? ☐ Yes, 1-2 times ☐ Yes, 3 times or more ☐ No

> If yes:

- Was it a: ☐ Nasopharyngeal swab ☐ Blood test (serology) ☐ Saliva swab
- Was the test? ☐ Positive ☐ Negative

> If positive: what was the date of the last positive test?

Day Month Year

---

25 How would you evaluate your risk of getting infected with Covid-19 compared to other people?

Risk: ☐ Very high ☐ High ☐ Similar ☐ Low ☐ Very low

---

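### Only test-positive patients without a form are phoned after the visit, and the 10-day exposure items put to them are not tied to the ED visit, so part of their exposure window can fall after diagnosis

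*Combined protocol and SAP*

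**What the plan says.** Protocol section 2.5 defines who is phoned: "For patients with a positive SARS-CoV-2 test and who have not completed the DEPIST-COVID self-administered questionnaire". For these patients, "a subsequent telephone follow-up will be performed to retrieve their profile based on the questions in the self-administered questionnaire". The synopsis names the same instrument for the control strategy: "Patients who have not completed it will be contacted by telephone to answer the DEPIST-COVID questionnaire by telephone". The chronology table in section 6.3.6 marks the call as a research procedure in both strategies: "For patients tested SARS-CoV-2+ who have not completed questionnaires: collection of data from the DEPIST-COVID questionnaire during a telephone call". No call is planned for test-negative patients, whose form belongs to the ED visit.

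On timing, section 6.1 gives "Duration of participation for a patient: 1 day (visit to the ED) + telephone call within 15 days", followed by ± 10. The synopsis (Research schedule) describes participation as lasting up to 15 days ± 10 for patients who are followed.

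In the questionnaire, items 14 to 24 stand under the heading "OVER THE LAST 10 DAYS". They cover masks, distancing, contact with a positive person, outings, transport, gatherings, hospitalisation and recent testing. Item 3 lies outside that block. It asks in the present tense, "Do you have symptoms suggestive of Covid-19", and then requests the date of first symptoms.

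Protocol section 13.2 and final SAP section 1.1 both use these data. In the SAP, among patients tested, "the exposure factors associated with the positivity of the SARS-CoV-2 test will be analysed using a generalised linear mixed model", with site as a random intercept. Final SAP section 1.5 adds that symptoms and exposure factors were not collected for control-period patients, or for intervention-period patients tested outside DEPIST-COVID screening.

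**The concern.** Whether a patient can be phoned depends on the test result, which is the outcome of the exposure model. If the items are read out as printed, a phoned case describes the 10 days before the call, while a test-negative patient describes the 10 days before the visit. That is measurement error that differs by outcome status.

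The error also has a predictable direction. After a positive result, sections 2.5 and 6.3.3 arrange isolation advice, contact tracing and testing of household members. Reported work outings, transport and gatherings (items 18 to 22) would tend to fall in phoned cases, which would make these exposures look protective. Contact with a positive person (item 17) could rise through household members found positive afterwards. Items 23 and 24 could pick up the admission and the test that belong to the index visit. Each of these is a consequence of the diagnosis that would enter the model as a candidate cause.

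Item 3 has a separate timing problem. Asked by phone, it refers to the day of the call and not to the day of the test, which matters for the planned proportion of asymptomatic patients among positives.

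**Working it through.** The plan gives no figure for the overlap between the recall window and the period before the visit, so there is nothing of its own to reproduce.

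**Inputs.** Recall window: 10 days (questionnaire, items 14 to 24). Call day d after the visit: 15 ± 10, that is day 5 to 25 if read as a target with a tolerance (section 6.1); earlier days are possible if it is read as an upper limit (synopsis). The documents give no distribution of call days, so even spread is an assumption.

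**Share of the window after the visit.** The window runs from day d − 10 to day d, so the share is min(d, 10)/10.

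| Call day | Window | Share after visit |
|---|---|---|
| 0 (form completed in ED) | −10 to 0 | 0% |
| 5 | −5 to +5 | 50% |
| 8 | −2 to +8 | 80% |
| 10 | 0 to +10 | 100% |
| 15 | +5 to +15 | 100% |

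**Averages under evenly spread calls.**
- Whole days 5 to 25: (0.5 + 0.6 + 0.7 + 0.8 + 0.9 + 16 × 1)/21 = 19.5/21 = 93%. On 16 of the 21 call days the whole window follows the visit.
- Days 0 to 25, continuous: (5 + 15)/25 = 80%.
- Days 0 to 15, continuous: (5 + 5)/15 = 67%.
- Days 0 to 5, continuous: 1.25/5 = 25%.

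**Illustration of bias.** Take an exposure with no true effect and 50% prevalence. Let a fraction f of cases be phoned, with exposure prevalence e in the period they describe. Prevalence among cases is then p = (1 − f) × 0.5 + f × e. The odds are 1 in the negatives, so the odds ratio is p/(1 − p). Both f and e are assumed.

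| f | e = 0.10 | e = 0.25 |
|---|---|---|
| 0.10 | 0.46/0.54 = 0.85 | 0.475/0.525 = 0.90 |
| 0.20 | 0.42/0.58 = 0.72 | 0.45/0.55 = 0.82 |
| 0.50 | 0.30/0.70 = 0.43 | 0.375/0.625 = 0.60 |

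**Sensitivity of a reported comparison.** In Table E1 the 10-day contact item is positive in 55/185 new diagnoses and 796/3,615 negatives, a difference of 7.7 points (1.4 to 14.8). The Miettinen-Nurminen method reproduces that interval. With three case answers changed from yes to no (52/185), the difference is 6.1 points and the lower limit is −0.06. This does not show that any answer came by phone. It shows that a few such answers could decide whether the interval excludes zero.

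**Search for a safeguard.** The protocol and both versions of the analysis plan give no reference date for phoned items. The questionnaire's staff pages have no field for mode or date of completion, and no analysis separates phoned from ED-completed forms.

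**The case against.** The strongest reply concerns reach. Final SAP section 1.5 removes the groups most likely to lack an ED form. Table H1 counts 3,943 new diagnoses and Table E1 only 224 through screening, so 3,719 of 3,943 (94%) lie outside these data. What remains is screened positives without a form. This stands.

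The timing can also be read more kindly. The wording allows calls before day 5, when most of the window still precedes the visit. No phone script is shown, and section 2.5 says only that the call is based on the questionnaire, so verbatim use of the 10-day heading is an inference. Both points stand. They make the size uncertain, but they do not supply the missing reference date.

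Table E1 shows no sign of heavy phone completion. The contact item is missing for 39/224 cases (17%) and 353/3,968 negatives (9%); routine recovery of cases by phone would tend to narrow that gap. The table labels the testing item as ever having been tested, and the six cases with a dated prior positive have a first quartile of 103 days, so there is little trace of the index test. Outings, transport and gatherings are not in the table, though contact is. The 50% scenario above therefore has no support in the documents.

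The later Changes to the analysis plan section describes the model for new diagnoses with patient characteristics as fixed effects. It does not exclude the exposure items.

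A reader might infer that symptoms, too, are asked over the last 10 days, and that asymptomatic status at testing is lost for phoned cases. The questionnaire does not support this. Item 3 asks for a calendar onset date, and the nurse records the test type, which was to follow symptom status at the visit; in Table E1, 90.1% of multiplex and 7.4% of rapid molecular patients reported symptoms. Timing is partly recoverable.

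**Conclusion.** The point holds as a gap in a secondary analysis that should be closed. The plan phones positives only, with items whose 10-day window is not tied to the visit, and then models those items against positivity. Asked as printed, the window is half post-diagnosis at day 5 and wholly so from day 10. The mean of 25% to 93% depends on the assumed spread of calls, and the odds ratios depend on an assumed share of phoned cases that the documents do not give.

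It would go too far to conclude that exposure data are mostly post-diagnosis for cases in general, or that the reported associations are wrong. Only screened positives without an ED form are affected, their number is unknown, and calls could have come early. The primary outcome rests on test results and patient flow and is untouched.

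**What to change.** - For phone completion, state that items 14 to 24 refer to the 10 days before the ED visit, with its date read out, and that item 3 refers to symptoms at that visit. The post-diagnosis share is then 0% for any call day.
- Record mode and date of completion for every form.
- In the SAP, rerun the exposure model without phone-completed forms as a sensitivity analysis. Once the phoned items are anchored, restricting the main model to ED-completed forms is a matter of preference.
- For data already collected without anchoring, use call records where they exist to identify phoned forms, exclude these from analyses of the 10-day items, and report how many there were.

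The cost is a line of interview wording, two data fields and a sentence in the SAP. The sensitivity analysis has slightly fewer cases, and some recall error remains in phoned answers even after anchoring.
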